### **Statistical analysis**

For each of the outcome variables that the visual analysis indicates a potential functional effect, a quantitative analysis will be performed to estimate the effect size. This analysis will be performed for each variable at which a significant trend is shown as described in the previous section. In order to estimate the individual-level effect sizes, we will use three different methods, as suggested by 'What Works Clearinghouse' (50), the standardized mean difference (Cohen's  $d$ ), the standardized mean difference with correction for small sample sizes (Hedges'  $g$ ) and piecewise regression analysis which does not only reflect the immediate intervention effect, but also the intervention effect across time. Multilevel modelling, which is recommended by the 'What Works Clearinghouse' and the single case educational design, specific mean difference index will be used to estimate the magnitude of the effect across cases and compared to the effect obtained by the single level estimates (77). For all the different neurophysiological parameters and clinical conditions, evaluated separately, the null hypothesis is that "there is no improvement from the proposed intervention", thus participants' responses are independent from the condition (baseline versus intervention) under which they were observed. The alternative hypothesis is that "the neurophysiological parameters and /or the clinical condition of the participants will be affected by the specific intervention", again assessed separately. We will reject the null hypothesis if the  $p$  value is smaller than 0.05. All tests will be two sided. Statistical analyses will be performed using the statistical software R (<https://www.r-project.org/>).

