## **Analysis plan**

To investigate possible effects of our protocol we will follow recommended guidelines (77), in which we will perform a separate analysis for each of the outcome measures, in all experimental phases (i.e., baseline, intervention and follow up). We will perform a visual analyses first, in order to determine whether there is a functional relationship between the intervention and the outcome measures, and secondly, we will perform a quantitative analysis methods to evaluate the magnitude of the intervention effect, provided there is evidence from the visual analyses (77). We will perform all neurophysiological and clinical assessments to each participant according to the number of data points during each phase (i.e., baseline, intervention, follow up) (see Figure 1).

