### **Visual analysis**

Two assessors will systematically measure each outcome measure across time, inter-assessor agreement will be calculated on at least twenty percent of the data points in each condition. The minimum acceptable inter-assessor agreement will be set to 0.8 (50). Initially, a visual analysis will be conducted and presented graphically in a spaghetti plot, in order to define whether there is a functional relation between the intervention and the outcome measures (77). During the visual analysis, six features of the research design graphed data will be examined: level, trend, stability, immediacy of the effect, overlap, and consistency. Over the within-phase examination an evaluation of level, trend and stability will be examined. Level will be reported from the mean score of each dependent variable and trend will determine whether the data points

are monotonically decreased or increased. Stability will be estimated based on the percentage of data points falling within 15% of the phase median, if this is higher than 80% then we assume that this criterion is met. Additionally, over the between-phase examination an evaluation of overlapping data among baseline and intervention phases, consistency of data patterns and immediacy of effect will be performed (77). The Percentage of Non-overlapping Data index will be used to quantify the proportion of data points in the intervention phase that do not overlap with the baseline phase (86) and the test statistic will be calculated using the Improvement Rate Difference as an effect size index. Immediacy of the effect will be examined by comparing changes in level between the last three data points of one phase and the three first data points of the next phase. Furthermore, consistency of data patterns involves the observation of the data from all phases within the same condition, with greater consistency expressing greater causal relation. Each feature will be assessed individually and collectively across to all participants and to all phases. Consequently, if the intervention protocol is the sole determinant of improvement, we expect to find indicators of improvement only at the intervention phase.

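### Standardised effect sizes, model estimates and p values are planned only for outcomes that first look positive on visual analysis of the same data, and the condition is worded in two ways that do not agree

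*Protocol*

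**What the plan says.** The protocol states the condition three times.

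- **Analysis plan.** Visual analysis comes first. The quantitative analysis of magnitude follows "provided there is evidence from the visual analyses".
- **Statistical analysis, first sentence.** The quantitative step applies to the "outcome variables that the visual analysis indicates a potential functional effect, a quantitative analysis will be performed to estimate the effect size".
- **Statistical analysis, second sentence.** "This analysis will be performed for each variable at which a significant trend is shown as described in the previous section".

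The same section then lists what the quantitative step contains: Cohen's d, Hedges' g, piecewise regression, a multilevel model across cases, and a two-sided test at 0.05 for each outcome.

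The Visual analysis section names six features: level, trend, stability, immediacy, overlap and consistency. On trend it says only that "trend will determine whether the data points" move monotonically up or down. The only numeric cut-off among the features is for stability: the share of points within 15% of the phase median, where "if this is higher than 80% then we assume that this criterion is met". Overlap is used to "quantify the proportion of data points in the intervention phase that do not overlap with the baseline phase". The section gives no test of trend and no rule for turning the six features into a pass or a fail.

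**The concern.** The visual step and the quantitative step use the same series and the same contrast. Level, overlap and immediacy between baseline and intervention decide whether an outcome goes forward, and the test then asks whether responses differ between baseline and intervention. When an estimate is kept only because the data already looked favourable, its average exceeds the true value, and its p value no longer has its nominal meaning.

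The condition also cannot be applied consistently as written. Two consecutive sentences give different criteria, and the second points back to a significance rule for trend that the preceding section does not contain. With no overall pass rule either, which outcomes are tested is settled by judgement after the data are seen.

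Nothing exempts the primary outcomes (resting motor threshold, MEP amplitude and CMCT), so the primary hypothesis could end without a standardised estimate or a test.

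**Working it through.** **No figure to reproduce.** The protocol gives no expected effect, SD or power for this step, so the size of the problem can only be illustrated.

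**Inputs from the protocol.** Five participants per subgroup (Study design). Five intervention and three follow-up time points (TMS measures analysis). Two-sided alpha of 0.05 per outcome (Statistical analysis).

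**Assumptions.** The baseline count is in a figure that is not shown, and the pass rule is not stated. Within-person SD is set to 1. Two families of pass rule were simulated:

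- *Level rule:* mean level improves in at least 4 of 5, or in 5 of 5, participants. Baselines of 5 to 9 points, independent errors, pooled within-participant test.
- *Overlap rule:* at least 3 of 5 participants have non-overlap of 50% or more, with or without a positive immediate change (lenient), or 70% or more with a positive immediate change (strict). Baselines of 3 to 7 points or 5 each, lag-1 autocorrelation 0 or 0.3, one-sample t test on the five differences as a stand-in for the multilevel model.

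**Formula.** Estimate = (1/5) × Σ(intervention mean − baseline mean) over the five participants. Bias = mean of the estimate among outcomes that pass − true shift.

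**Estimates among outcomes that pass**

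| Pass rule | True shift (SD) | Mean reported (SD) | Pass rate |
|---|---|---|---|
| Level, 4 of 5 / 5 of 5 | 0 | about 0.32 / 0.48 | 19% / 3% |
| Level, 4 of 5 / 5 of 5 | 0.30 | about 0.46–0.47 / 0.59–0.60 | – |
| Level, 4 of 5 / 5 of 5 | 1.0 | 1.01 / 1.06 | – |
| Level, 4 of 5 / 5 of 5 | 1.5 | 1.50 / 1.51 | – |
| Overlap, lenient | 0.5 | 0.82–0.92 | 7–14% |
| Overlap, lenient | 1.0 | 1.18–1.21 | 37–49% |
| Overlap, lenient | 1.5 | 1.56–1.58 | 78–82% |
| Overlap, strict | 0.5 | 0.93–1.10 | 0.5–2% |
| Overlap, strict | 1.0 | 1.33–1.37 | 8–17% |
| Overlap, strict | 1.5 | 1.67–1.69 | 39–51% |

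In relative terms, a true 0.5 SD is overstated by between 0.82/0.5 − 1 = 64% and 1.10/0.5 − 1 = 120% under the overlap rules. A true 1.5 SD is overstated by 1.56/1.5 − 1 = 4% to 1.58/1.5 − 1 = 5% under the lenient overlap rule.

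**p values among outcomes that pass, no true effect.** 12% (4 of 5) and 35% (5 of 5) are below 0.05 under the level rules. Under the lenient overlap rules the figure is 14–30%, imprecise because only 23 to 121 simulated outcomes passed per setting.

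**Overall error, no true effect.** Passing and rejecting together: 0.19 × 0.12 = 2.3%, or 0.03 × 0.35 = 1.1%, under the level rules; at most about 0.4% under the overlap rules. All are below 5%.

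**Real effects left untested.** At a true 1.0 SD, 22–42% of all simulated outcomes under the lenient overlap rules, and 44–68% under the strict one, would reach p < 0.05 but fail the visual step.

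**Without the condition.** In the overlap-rule simulations, mean estimates match the true shift to within about 0.01 SD, and rejection under no effect is 4.8–5.4%.

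**The case against.** **Failing outcomes are not left empty.** A reader might infer that they get no estimate and vanish from the report. The protocol does not support that. The Clinical measures analysis section calculates phase means and their differences for every clinical measure and the fatigue scale, and the TMS measures analysis section does so for resting motor threshold and CMCT, all unconditionally. Percentage of Non-overlapping Data and the Improvement Rate Difference, which the protocol calls an effect size index, belong to the visual step and so precede the condition. This stands and limits the point to what is missing: standardised and model-based estimates, any stated uncertainty, and p values.

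**Type I error.** A reader might infer that the condition inflates false positives. It does not. Requiring two hurdles makes a positive claim harder for each outcome. The excess over 5% exists only among outcomes that pass.

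**Flat level shifts.** Taken alone, the trend sentence suggests that a clean shift between two flat phases would be excluded. The Visual analysis section weighs six features individually and collectively, and level, overlap and immediacy all register such a shift. Monotonicity is not stated as a pass condition. The sentence is ambiguous; the exclusion is not established.

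**Stability.** With five points, more than 80% means all five, since 4/5 is exactly 80%. But failing stability is not said to block the analysis, so no change to that threshold is proposed.

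**The simulated rules are assumed.** This stands. None of them appears in the protocol, and under the level rules the bias at 1.0 SD is only 0.01 to 0.06 SD. The direction does not depend on the rule chosen; the size does.

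**Visual-then-quantitative order follows a cited guideline.** That source cannot be checked here. The order is not the defect; making estimation depend on the visual verdict is.

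**Detail may sit in an analysis plan.** A pass rule might. The condition itself, and its two conflicting wordings, are in the protocol.

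**Conclusion.** The concern holds in a limited form. The protocol makes its standardised and model-based effect sizes and all its tests at 0.05 conditional on a favourable visual reading of the same contrast, and words that condition in two ways that do not agree. Estimates for outcomes that pass will be too large on average, their p values cannot be taken at face value, and real effects can go untested.

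The size is uncertain because it rests on assumed pass rules, baseline lengths and error structure. It is large for null or small effects: a true 0.3 SD becomes about 0.46 to 0.60 under the level rules, and a true 0.5 SD about 0.8 to 1.1 under the overlap rules. It is small for large effects under lenient rules, at most about 5% at 1.5 SD. The documents do not support saying that failing outcomes receive no estimate of any kind, that overall type I error rises, or that flat level shifts are excluded.

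**What to change.** In the Analysis plan and Statistical analysis sections, remove the condition. State that the planned quantitative analysis (effect size, 95% confidence interval, p value) will be run and reported for every primary and secondary outcome whatever the visual verdict, with the visual analysis shown beside it. Delete the sentence that refers to a significant trend. Keep the visual analysis as planned.

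The cost is a change of wording, a little more analysis and longer results tables. No further data or participants are needed. The per-outcome false positive rate returns to its nominal 5% from the lower rate that the double hurdle implied.

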### **Study design**

Each subgroup includes five participants and each one constitutes a separate research study that follows a concurrent multiple baseline design across subjects, designed according to the 'What Works Clearinghouse' criteria for single case studies (50). During the experimental procedure, all participants will begin the study with the baseline phase at the same time while the intervention phase is introduced staggered across patients and time (see Figure 1). The intervention will be introduced systematically in one patient while baseline data collection continues in the others without any intervention. The cause-effect inference can be clearly verified by the staggered duration through separate baseline phases (51). Subsequently, if the intervention is the sole cause of improvement in participants' conditions, the proposed outcome measures will not change for the participants that remain in the baseline phase but will be improved only for those in the intervention phase.

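### One two-sided p<0.05 rule per outcome is attached to several individual and across-case analyses, and the protocol does not say which of them supplies the p value

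*Protocol*

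**What the plan says.** The protocol's Statistical analysis section lists the methods for any outcome that the visual analysis has flagged:

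- **Individual level:** "In order to estimate the individual-level effect sizes, we will use three different methods". These are Cohen's d, Hedges' g and "piecewise regression analysis which does not only reflect the immediate intervention effect, but also the intervention effect across time".
- **Across cases:** multilevel modelling and a mean-difference index, which "will be used to estimate the magnitude of the effect across cases and compared to the effect obtained by the single level estimates".

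The paragraph then gives one null hypothesis, applied to each outcome separately: that participants' "responses are independent from the condition (baseline versus intervention) under which they were observed". It is rejected if the p "value is smaller than 0.05", and "All tests will be two sided".

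The Study design section sets the unit: "Each subgroup includes five participants and each one constitutes a separate research study". The decision is therefore taken again for every outcome in every subgroup.

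The Analysis plan section puts the visual analysis first. The quantitative methods follow, to gauge the size of the effect, where the visual analysis supports one.

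**The concern.** The protocol fixes the threshold and lists the analyses but does not connect them. The p value in the rejection rule could come from one participant or from the pooled model. It could also refer to a difference in phase means, an immediate level change or a change in slope. No order of precedence is given, and comparing across-case with single-level results comes with no rule for when they disagree.

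Disagreement is foreseeable. A gain that builds over 12 weeks of training can appear in slope and not in immediate level. One strong responder among five can be significant alone and not in the pooled model. If the choice is left until the results are known, the same data could be reported as positive or negative, and the stated 5% would not describe the decision.

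This concerns several analyses of one outcome. It is separate from the number of outcomes tested.

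**Working it through.** The protocol gives no power or error-rate calculation, so there is no stated figure to reproduce.

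**Inputs from the protocol**
- Threshold 0.05, two-sided (Statistical analysis).
- Five participants per subgroup (Study design).
- Five intervention-phase time points (TMS measures analysis; assumed the same for clinical outcomes).
- Three individual methods, one of which has two effects, and two across-case methods (Statistical analysis).

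**Assumed inputs**
- Baseline lengths, because Figure 1 is not shown: 3-7, 5-9, or 5, 7, 9, 11 and 13 points.
- Independent normal errors, or lag-1 autocorrelation of 0.3.

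**Step 1: how many p values could there be for one outcome in one subgroup?** The protocol gives no count. It depends on what is counted:
- d and g merged, one p value per model: 5×2 + 2 = 12. Counting only the piecewise coefficients and two pooled piecewise terms, with no effect-size index treated as a test, also gives 5×2 + 2 = 12.
- Methods as listed, one p value each: 5×3 + 2 = 17.
- d and g merged, two piecewise effects, three across-case terms: 5×(1+2) + 3 = 18.
- d and g separate, two piecewise effects, three across-case terms: 5×4 + 3 = 23.

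If the tests were independent, the chance of at least one p<0.05 under no effect would be 1 − 0.95^k:
- k = 12: 0.46
- k = 17: 0.58
- k = 18: 0.60
- k = 23: 0.69

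**Step 2: allow for correlation between the tests.** Subgroups of five were simulated under no effect, without the visual screen. Each participant had a phase-mean t test and piecewise level and slope tests. Across cases, regressions with fixed participant effects stood in for the multilevel model and the index, giving pooled level, slope and phase-mean tests. Chance of at least one p<0.05 with independent errors, over the three baseline patterns:

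| Tests allowed to decide | Chance |
|---|---|
| One pooled phase-mean test | about 0.05 |
| Two pooled piecewise terms | 0.09-0.10 |
| Three pooled tests | 0.13-0.14 |
| Ten individual piecewise coefficients | 0.37-0.39 |
| All 18 | about 0.54 (0.52-0.55 across runs) |

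**Step 3: serial correlation.** With lag-1 autocorrelation of 0.3 that the model ignores, the single pooled phase-mean test rejects at 0.12-0.13. Naming one test therefore restores 5% only if autocorrelation is also handled.

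**Step 4: what the visual screen does to these figures.** The chance that an outcome passes the screen and also gives p<0.05 cannot exceed the chance that it gives p<0.05, so the Step 2 figures are upper limits on that joint chance for the assumed tests and errors. The rate among outcomes that do pass is the joint chance divided by the chance of passing, and can be higher. The Visual analysis section lists six features without saying how many must be met or how they combine, so neither quantity can be computed.

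**The case against.** **Estimation is the stated purpose.** The protocol introduces d and g as effect sizes and the across-case methods as measures of magnitude, so much of a descriptive labelling is already implied. This stands. It also means the phase-mean t tests simulated for each participant are stand-ins that the protocol does not name, and the figure for 18 tests rests partly on them. It does not settle the matter, because the same paragraph adds a null hypothesis, a p-value threshold and two-sided tests. Some listed analysis must supply the p value, and the figures for pooled and piecewise terms need no effect-size index to act as a test.

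**There is no rule that any one result suffices.** A reader might infer that an outcome is declared positive as soon as any of some 18 tests is significant, so that the plan's false-positive rate is about 54%. The document does not support this. It speaks of a single p value, phrases the null in terms of participants collectively, and compares baseline with intervention. The count of 18 is an assumption within 12 to 23. The supportable statement is that the deciding analysis is not named.

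**The visual analysis comes first.** This is true: an outcome with no visual indication is never tested, so a small p value alone cannot produce a positive claim. But the screen reads the same data and has no stated overall pass rule, so it cannot be credited with controlling the error rate.

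**This belongs in a statistical analysis plan.** Model detail often does, and only the protocol was available here. However, this protocol itself fixes the rejection rule beside the list of methods, and leaves the link between them open.

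**Conclusion.** The point holds as a badly fixed decision rule: one rejection rule per outcome, several analyses that could feed it, and no statement of which one decides or at what level.

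The size depends on how the rule is read. If only the two pooled piecewise terms compete, the chance of a nominally significant result under no effect is roughly twice the stated 5%. It is higher when individual coefficients may also count. These figures assume no visual screen, independent errors, five intervention points, assumed baseline lengths and fixed-effect stand-ins for the multilevel model. They illustrate what the wording permits and do not estimate the trial's error rate.

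The matter should be corrected before analysis. It is a repair of wording and does not undermine the single-case design.

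**What to change.** In the Statistical analysis section:

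1. Name one across-case multilevel model and one pre-stated baseline-versus-intervention contrast as the only source of the p value for each outcome and subgroup. One example is the intervention effect averaged over the 12-week phase. Another contrast would also serve; what matters is that one is chosen in advance.
2. Specify a small-sample degrees-of-freedom correction and a model for within-person autocorrelation.
3. State that Cohen's d, Hedges' g, the individual piecewise coefficients and the mean-difference index are descriptive, reported with confidence intervals and not used to reject the null.

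The methods are already planned, so this needs no new data, visits or participants. The cost is that no significance claim can be made for a single participant or a single coefficient. Individual results would still be shown and discussed.

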### **Treatment Fidelity**

Treatment fidelity will be monitored during the study to ensure that the exercise program and the outcome variables assessments will be executed as intended. This will allow us to truly test the effectiveness of our proposed protocol and hence, the danger to commit a Type 1 or Type 2 error will be reduced (87). A checklist will be developed to ensure that all the key elements of our study are implemented as planned. The assessors and the providers of the intervention protocol will undergo preparation to confirm their ability acquirement. During the intervention sessions, a supervisor will observe the procedure to confirm the constant and accurately administration of the intervention. During the different phases the patients will be closely monitored to identify possible ingredients that may influence the effectiveness of the intervention (e.g., changes in the pharmacological treatment, relapse, participation in other training programs, changes in their daily routine).

